#### Datasets

CPRD is the world’s largest computerized database of anonymized longitudinal medical records from primary care. Information includes records of symptoms, diagnoses, referrals, prescriptions issued in primary care, records of immunizations and vaccinations, laboratory test results, lifestyle information (eg smoking and alcohol status), and all other types of care administered as part of routine general practice. Currently, data are collected on over 5 million active patients from 674 general practices, covering around 6.9% of the UK population registered with a general practitioner [39].

Records for 3 population groups will be extracted from CPRD. The datasets will be structured as shown in Table 1.

#### Data Linkages

Electronically linked data for individuals in the study population will be obtained from the following sources: HES data for hospital admissions [41], ONS for dates and causes of death [42], and the Index of Multiple Deprivation (IMD) for area deprivation at practice and patient level [43].

#### Health and Health Care Outcomes

The following outcomes listed in Table 2, corresponding to the objectives described above, will be examined.

Analyses may be limited by the quality and availability of data for some of the above variables, but wherever possible, validated code lists will be employed.

**Table 1 table1:** Structure of the Clinical Practice Research Datalink datasets.

Dataset	Population	Specification	Estimated sample size of patients
Dataset A	Adults (≥18 years) with SMI^a^	Longitudinal health care records of adult patients with SMI defined as the presence of a clinical diagnostic code for schizophrenia, affective disorder (divided into bipolar or unspecified affective disorder), and other types of psychoses. Read codes previously tested and applied by the research team [37] will be used to identify the presence of SMI.	33,000
Dataset B (a subset of dataset A)	Adults with a diagnosis of SMI and diabetes mellitus	Diabetes, identified using previously tested and validated Read codes, will be further defined as the presence of a clinical diagnostic code for type 1 diabetes, type 2 diabetes, drug-induced diabetes, or unspecified diabetes. Individuals with a diagnostic code of gestational diabetes, cystic fibrosis, and hemochromatosis will be excluded.	3600 based on a predicted diabetes prevalence of 11.1% [40]
Dataset C (matched controls to dataset B)	Adults with a diagnosis of type 2 diabetes but without SMI	Patients with type 2 diabetes in dataset B will be matched by Clinical Practice Research Datalink to a cohort of patients who have a diagnosis of type 2 diabetes but without SMI (controls) with a case to control ratio of 1:4 on the basis of age, gender, and practice.	14,400

^a^SMI: severe mental illness.

**Table 2 table2:** Health and health care outcomes corresponding to objectives.

Outcome	Objective #
Diabetes status and onset	1
Diabetic and cardiovascular control (measured by recorded hemoglobin A_1c_, blood pressure, and cholesterol levels)	2
Diabetic complications: acute hyperglycemic events, hypoglycemia, microvascular complications (retinopathy, neuropathy, and nephropathy)	2, 4
Diabetic complications: macrovascular complications (coronary artery disease, cerebrovascular disease, and peripheral arterial disease)	2, 3, 4, 7
Hospital admissions for the above conditions	2, 3, 4, 7
Mental health outcomes including severe mental illness relapses (measured by hospital admissions and general practitioner referrals to community mental health teams or crisis teams) and markers of depression or anxiety (ie, general practitioner diagnoses or prescriptions for antidepressants)	2, 3, 4, 7
Mortality	2, 3, 4, 7
Health care utilization (including the number and type of primary care consultations) and costs	6
Health care interventions (eg, first and second generation antipsychotic and antidiabetic medications, care pathways, and referrals)	6, 7

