#### Risk Factors and Explanatory Variables

Known risk factors and covariates for developing diabetes and diabetes complications will be included in the analyses to determine their relative association with the development and progress of diabetes in people with SMI. The list of factors will be determined by evidence synthesis, complemented by expert consensus, and will be responsive to emerging findings from the qualitative interviews.

The candidate risk factors include patient demographics and socioeconomic markers (sex, age, ethnic group, area deprivation, and rurality), lifestyle (obesity, smoking, and alcohol consumption), social vulnerability markers such as housing status, hyperlipidemia, family history, type of SMI and diabetes (including order and timing of diagnosis), length of diagnosis, illness severity, and multimorbidity.

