All statistical models will include a set of relevant patient, local population, and practice covariates where possible to control for confounding and interacting influences potentially masking the relationship between diabetes management and outcomes.

In sensitivity analyses, noncompliance (including refusal of treatment, informed dissent, and nonattendance) will be included as an independent variable in the models. Sensitivity analyses will be conducted with noncompliance treated as either a time-dependent (*expiring*) or time-independent (*nonexpiring*) variable and as specific to the refused treatment or as a general marker of noncompliance. Noncompliance will be used to create *offer of treatment* explanatory variables, facilitating *intention-to-treat* type analyses.

Robustness checks will be carried out to ensure our results are reliable, and plausibility tests to ensure findings are meaningful in practice and can inform policy. Model assumptions will be checked for all analyses, and if they are in doubt, the data will be transformed before analysis or alternative nonparametric analysis methods will be used.

**Table 3 table3:** Summary of statistical analysis plan by study objective.

Objective #^a^	Description	Datasets	Variables	Analysis
1	The impact of key explanatory variables on both diabetes status and time to onset of diabetes	Quantitative dataset A (people with SMI^b^)	Explanatory variables: sociodemographic characteristics, medication use, physical and mental health status, family history of diabetes, biometric data dysregulation, and lifestyle factors	Multilevel modeling: logistic model (diabetes status) and survival model (time to diabetes onset)
2	The impact of key explanatory variables (as above) on diabetes and mental health outcomes	Quantitative dataset B (people with SMI and type 2 diabetes)	Outcomes: diabetic and cardiovascular control; diabetic complications; hospital admissions; mental health outcomes, for example relapses and episodes of depression and anxiety and mortality	Repeated measures mixed models: linear, logistic, and survival models
3	The impact of diabetes status and other explanatory variables (as above) on physical and mental health outcomes	Quantitative dataset A	Outcomes: macrovascular diabetic complications, hospital admissions, mental health outcomes, and mortality	Poisson or negative binomial multilevel models for count outcomes, logistic multilevel models for binary outcomes

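### Objective 1 concerns the development of diabetes, but its logistic model of diabetes status runs on all of dataset A, so people whose diabetes came before SMI or before observation count as cases

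*Protocol article*

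**What the plan says.** The Objectives section words objective 1 as finding factors associated with developing diabetes among people with SMI. The overall aim speaks of determinants, and Table 3 describes the objective as "The impact of key explanatory variables on both diabetes status and time to onset of diabetes".

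Table 3 names dataset A as the data for this objective, with two multilevel models: logistic for diabetes status and survival for time to onset. The explanatory variables in that row include medication, physical and mental health status, biometric measures and lifestyle, all of which can change after a diabetes diagnosis.

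Table 1 (under Health and Health Care Outcomes) defines dataset A by an SMI code alone: "Longitudinal health care records of adult patients with SMI defined as the presence of a clinical diagnostic code for schizophrenia", or the other listed SMI diagnoses. Its expected size is 33,000. Dataset B is the part of A that also has diabetes, in either order of diagnosis, and its size is given as "3600 based on a predicted diabetes prevalence of 11.1" percent. Table 1 excludes certain codes from the diabetes definition (gestational diabetes, cystic fibrosis, hemochromatosis). Diabetes that predates SMI or follow-up is not among the exclusions.

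The section on Risk Factors and Explanatory Variables lists "type of SMI and diabetes (including order and timing of diagnosis), length of diagnosis" among the candidates. Patients with diabetes first are therefore expected in the data.

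**The concern.** A person can develop diabetes as an observed person with SMI only if they do not already have it when that observation starts. A model of diabetes status on all of dataset A ignores this. Take a hypothetical patient with diabetes coded in 1995 and a first schizophrenia code in 2008. That patient has status equal to 1 and is a case in the logistic model. Yet the SMI diagnosis, and any treatment or mental-health measure recorded from 2008 on, came after the outcome.

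Two distortions can follow. Earlier cases whose exposure has nothing to do with their diabetes dilute a real association. Earlier cases whose medication, biometric values or health status changed because of diabetes create or inflate one. Both affect the objective that serves the study's leading aim, and the results are meant to feed recommendations for interventions. Factors fixed early in life, such as sex, ethnic group and family history, are not open to this reversal of time order.

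**Working it through.** **1. The plan's own figures.** Inputs from Table 1: 33,000 people in dataset A and a prevalence of 11.1%. 33,000 × 0.111 = 3,663, against 3,600 stated (63 / 3,663 = 1.7% lower). The figure reproduces within rounding, and it is a count of prevalent cases. It does not separate onset during follow-up from diabetes already present.

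**2. What would be needed for all 3,600 to be new.** The Statistical Analysis section expects about 5 to 6 years of data per person. At 5.5 years, 33,000 × 5.5 = 181,500 person-years, and 3,600 / 181,500 = 19.8 new cases per 1,000 person-years. At 6 and 5 years the rate is 18.2 and 21.8. This is crude, because it counts person-time after diabetes. The article gives no incidence to compare it with, so the share of earlier cases is unknown and is assumed below.

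**3. Dilution.** Assume a true odds ratio of 2.0, 60% exposed among non-cases (odds 1.5), and exposure unrelated to diabetes among earlier cases (also 60%). Incident cases then have exposure odds 2.0 × 1.5 = 3.0, that is 75%. With share p of earlier cases among all cases:

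exposure in cases = (1 − p) × 0.75 + p × 0.60; estimated odds ratio = odds of that / 1.5

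- p = 0.10 (360 of 3,600): 0.735; 0.735 / 0.265 = 2.774; odds ratio 1.85
- p = 0.25 (900): 0.7125; 0.7125 / 0.2875 = 2.478; odds ratio 1.65
- p = 0.40 (1,440): 0.690; 0.690 / 0.310 = 2.226; odds ratio 1.48

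**4. The other direction.** Assume a factor with no true effect and 30% prevalence (odds 0.3 / 0.7), which is more common after diabetes among earlier cases. With share s of earlier cases and prevalence q in them:

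prevalence in cases = (1 − s) × 0.30 + s × q

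- s = 0.10, q = 0.40: 0.31; odds ratio 1.05
- s = 0.30, q = 0.50: 0.36; odds ratio 1.31
- s = 0.50, q = 0.60: 0.45; odds ratio 1.91

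Steps 3 and 4 together show that the same design flaw can pull an estimate towards the null or away from it.

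**5. After restriction.** Removing earlier cases at p = 10%, 25% and 40% leaves 3,240, 2,700 and 2,160 cases among 32,640, 32,100 and 31,560 people at risk.

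**The case against.** The strongest reply is that this is a condensed article. Table 3 is offered as an outline, and cohort-entry rules, time origin and covariate timing usually sit in a fuller document. Table 1 describes data extracts, and dataset A must contain people with existing diabetes because objective 3 compares people with SMI who do and do not have it. Table 3 also narrows a dataset elsewhere: it describes dataset B for objective 2 as type 2 diabetes, while Table 1 admits other types.

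Part of this stands. A reader might infer that the survival model carries the same error. The article says only that it models time to onset. It gives neither risk set nor time origin, and a usual survival set-up drops people whose event precedes entry. A reader might also infer that order of diagnosis will be entered as a predictor for objective 1, where it would be built from the outcome. The candidate list serves both developing diabetes and its complications, the same phrase includes type of diabetes, and the objective 1 row of Table 3 does not name order. The text supports neither inference.

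The reply does not rescue the logistic model. For objective 1, Table 3 names dataset A as the analysis data and diabetes status as the outcome. That is a stated choice, and it does not match an objective about development. The index date mentioned under Statistical Analysis concerns matching and does not define a diabetes-free cohort.

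It is also fair that objective 1 says only associated with. The words determinants and impact elsewhere go further, and even an association with development needs people who could still develop the disease.

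**Conclusion.** The point holds for the logistic model of objective 1. As stated, it counts as cases people who were never at risk of onset as observed persons with SMI, and it allows values recorded after diabetes to be estimated as determinants of it.

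Neither the size nor the direction of the bias follows from the article. Under the assumptions of step 3, a true odds ratio of 2.0 falls to between 1.85 and 1.48. Under those of step 4, a null factor appears with an odds ratio of 1.05 to 1.91. The shares, exposure prevalences and true effects are all assumed. A reader might conclude that true associations would be reversed, but none of these calculations shows that.

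For the survival model and for order of diagnosis, the article establishes no error. An explicit statement on each is enough.

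**What to change.** - For objective 1, restrict both models to people in dataset A with no diabetes code at entry. Define entry as the latest of the first SMI code, 1 April 2000, age 18 and the start of up-to-standard registration.
- Measure explanatory variables before onset, either at entry or as time-updated values.
- State that order of diagnosis is used only in objectives where everyone in the analysis has diabetes.

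Dataset A can stay as extracted, since objective 3 needs people with existing diabetes. The change is to the analysis definition and needs no new data. The cost is fewer objective 1 cases than the 3,600 in dataset B, by a number the article does not allow one to state. The cases lost could not have informed onset.

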#### Risk Factors and Explanatory Variables

Known risk factors and covariates for developing diabetes and diabetes complications will be included in the analyses to determine their relative association with the development and progress of diabetes in people with SMI. The list of factors will be determined by evidence synthesis, complemented by expert consensus, and will be responsive to emerging findings from the qualitative interviews.

The candidate risk factors include patient demographics and socioeconomic markers (sex, age, ethnic group, area deprivation, and rurality), lifestyle (obesity, smoking, and alcohol consumption), social vulnerability markers such as housing status, hyperlipidemia, family history, type of SMI and diabetes (including order and timing of diagnosis), length of diagnosis, illness severity, and multimorbidity.

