## Abstract

**Background:**

The average life expectancy for people with a severe mental illness (SMI) such as schizophrenia or bipolar disorder is 15 to 20 years less than that for the population as a whole. Diabetes contributes significantly to this inequality, being 2 to 3 times more prevalent in people with SMI. Various risk factors have been implicated, including side effects of antipsychotic medication and unhealthy lifestyles, which often occur in the context of socioeconomic disadvantage and health care inequality. However, little is known about how these factors may interact to influence the risk of developing diabetes and poor diabetic outcomes, or how the organization and provision of health care may contribute.

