## Introduction

### Background

Severe mental illness (SMI) refers to a set of disabling conditions such as schizophrenia, schizoaffective disorder, or bipolar disorder. People with SMI, who account for around 1% of the population [1], may experience feelings of persecution, hallucinations, problems with mood, impaired cognition, and lack of motivation. These difficulties can have an adverse impact on several areas of life such as housing, employment, relationships, and personal care, which can, in turn, increase the likelihood of mental and physical health problems. They have a reduced life expectancy, living for 15 to 20 years less than the population as a whole, and experience poorer health outcomes [2-5].

Diabetes is a significant contributor to the increased morbidity and mortality experienced by people with SMI. The condition is 2 to 3 times more prevalent in this population [6-8], and complications of diabetes are higher than for people without SMI [9,10]. The link between the metabolic side-effects of antipsychotic medication and diabetes has been well-documented [11-13], but there are additional complexities; other work points to the possibility of a genetic neuroinflammatory mechanism predisposing people toward both conditions [14], which could explain the occurrence of the comorbidity independent of antipsychotic medication [15,16]. Furthermore, other factors have been implicated such as lifestyle health risk factors such as diet [17], smoking [18,19], low levels of physical activity [20], and higher levels of other comorbid conditions [21]. However, little is known about the relative contribution of these factors, or about possible synergistic relationships that may increase the risk of people with SMI developing diabetes or experiencing poorer diabetes outcomes.

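### Objective 1 files obesity under lifestyle and models it beside medication use, so any antipsychotic effect that runs through weight can be read as lifestyle

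*Protocol article*

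**What the plan says.** The abstract names "side effects of antipsychotic medication and unhealthy lifestyles" as two of the suspected reasons for diabetes in people with SMI. The Introduction (Background) says "The link between the metabolic side-effects of antipsychotic medication and diabetes has been well-documented". It then turns to lifestyle as a further group of factors, giving diet, smoking and low physical activity as examples. Obesity is not among them.

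The section Risk Factors and Explanatory Variables builds the group differently: "lifestyle (obesity, smoking, and alcohol consumption". Diet and physical activity are not named. The purpose of including the factors is "to determine their relative association with the development and progress of diabetes in people with SMI". The list is provisional: "The list of factors will be determined by evidence synthesis, complemented by expert consensus". Medication is not on it.

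Medication enters through Table 3 (Statistical Analysis). For objective 1 the explanatory variables include "medication use, physical and mental health status, family history of diabetes, biometric data dysregulation, and lifestyle factors". The models are a multilevel logistic model for diabetes status and a survival model for time to onset. The article does not say when obesity is measured relative to antipsychotic start, or whether medication is also modelled without obesity.

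**The concern.** Obesity is a bodily state, not a behaviour. Diet and inactivity contribute to it, and a metabolic side effect of medication may do so too. If it is, it lies on the path from medication to diabetes. Adjusting for it then turns the medication coefficient into a direct association, with the weight pathway taken out.

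The label decides how that removed part is reported. Under a lifestyle heading, excess obesity that follows medication looks like behaviour. The article sets out to compare the relative association of the factors and to turn findings into recommendations for interventions and services. Whether an association is attributed to medication or to behaviour would bear on those recommendations.

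**Working it through.** **Figures in the article.** The point rests on no stated effect size or power figure. The one figure used below is the 11.1% diabetes prevalence in Table 1. It reproduces the stated sample size closely: 33,000 × 0.111 = 3,663, against 3,600 stated.

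**Reading the sections together.**
1. The Background keeps the medication route and lifestyle apart.
2. The candidate list puts obesity in lifestyle.
3. Table 3 lists medication use and lifestyle factors together for the same models.
4. Nothing stated dates obesity or plans a medication estimate without it.

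**Illustration.** Apart from the 11.1%, all inputs are assumptions that the documents do not give: half of patients exposed to antipsychotics, obesity 25% in the unexposed and 40% in the exposed, odds ratio 3 for obesity, and a direct odds ratio of 1.2 for medication.

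The baseline odds that give 11.1% overall are 0.0709. Diabetes risk in each cell is odds/(1 + odds):
- unexposed, not obese: 0.0709/1.0709 = 0.0662
- unexposed, obese (odds × 3): 0.1755
- exposed, not obese (odds × 1.2): 0.0785
- exposed, obese (odds × 3.6): 0.2034

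Averaging over obesity:
- unexposed: 0.75 × 0.0662 + 0.25 × 0.1755 = 0.094
- exposed: 0.60 × 0.0785 + 0.40 × 0.2034 = 0.128

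Using unrounded risks (0.0936 and 0.1284), the medication odds ratio without obesity is (0.1284/0.8716)/(0.0936/0.9064) = 1.43. Within each obesity stratum it is 1.20. The share of the log odds ratio removed is 1 − ln 1.20/ln 1.43 = 1 − 0.182/0.356, or about 49%.

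A simulation of 400,000 people on the same assumptions agrees to within sampling error:

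| Obesity in exposed (25% in unexposed) | Medication OR, no obesity term | With pre-treatment obesity | With current obesity | Share of log OR removed by current obesity |
|---|---|---|---|---|
| 25% | 1.19 | 1.20 | 1.20 | none |
| 30% | 1.27 | 1.28 | 1.21 | 23% |
| 40% | 1.41 | 1.42 | 1.18 | 51% |
| 50% | 1.58 | 1.59 | 1.19 | 63% |

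Over the 30% to 50% rows, the share removed is 11% to 40% if the direct odds ratio is 1.5, and essentially all of it if the direct odds ratio is 1.0.

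**Is the absence of diet and activity the cause?** A diet/activity variable was added that raises both obesity and diabetes (log odds of obesity +0.7 per SD, diabetes odds ratio 1.3 per SD; exposed obesity set to 40% at the average value). The medication odds ratio was 1.41 without obesity and 1.17 with current obesity. With diet/activity in the model as well it was 1.20. Measuring diet and activity recovers 0.03 of a fall of 0.24, so nearly all of the fall comes from adjusting for the intermediate.

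**The case against.** The strongest reply is that this criticises a model the article does not fix. The factors are candidates, Table 3 is a summary, and the timing and coding of obesity are details that an article may leave to the full plan. This stands against any claim that bias will occur. It does not answer the classification itself, which is printed and departs from the article's own Background. That Background list is introduced as examples, so it does not formally exclude obesity, but it does show what the article means by lifestyle.

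Four further points stand in whole or part:
- **Emphasis.** The wording of objective 1 does not name medication; only Table 3 adds it. A reader might infer that ranking medication against lifestyle is a main product of objective 1. The article speaks of relative association across all factors and plans no such two-way ranking.
- **Biometric data.** Table 3 lists biometric data dysregulation separately, and weight might be handled there. That would change the label. The medication coefficient would still be adjusted for the intermediate.
- **Data limits.** The Datasets section gives smoking and alcohol as its examples of lifestyle information in CPRD. Diet and activity may be left out because they are not recorded.
- **Pre-treatment obesity as the main covariate.** It has no natural date for people never prescribed an antipsychotic. With an anticipated 5 to 6 years of data per person, it may often be missing for users too. It can support a sensitivity analysis but not the main model.

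**Conclusion.** The point holds as a conditional one. The article classes obesity as lifestyle and lists it beside medication use for objective 1, without saying that it may be an intermediate. If the obesity record postdates antipsychotic start and both terms are in one model, the medication coefficient is a direct association only, and the remainder can be read as lifestyle.

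Two stronger readings are tempting and not supported. The first is that medication's share of diabetes risk is understated as planned, by some stated amount. The article fixes neither the timing of obesity nor the final model. It speaks of metabolic side effects and does not mention weight gain, so no size can be derived from it. The fall from about 1.4 to 1.2 rests entirely on the assumed inputs, and there is no loss if medication does not alter obesity. The second is that the label, or the missing diet and activity measures, produces the understatement. The label changes no coefficient, and the missing measures move the medication estimate very little. Their consequence is that obesity stands in for behaviours that are not measured, which makes a lifestyle result hard to interpret.

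**What to change.** 1. In Risk Factors and Explanatory Variables, list obesity separately from lifestyle, as a possible intermediate between medication and diabetes.
2. For objective 1, report the medication association without obesity (total) and with obesity (direct), side by side.
3. The model without obesity leaves any confounding by obesity that preceded treatment. As a sensitivity analysis, adjust for obesity recorded before antipsychotic start where such a record exists, with a defined index date for people never prescribed an antipsychotic.
4. If diet and physical activity are not recorded, state that their contribution is not estimated, and keep the word lifestyle for behaviours that are recorded.

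The cost is one extra model, the work of setting an index date for never-users, a change of wording, and wider intervals in the subset with a pre-treatment record.
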